**Figure 2 figure2:**
[figure not shown]
Flow of participants.

### Sample Size Calculation

To detect a difference in change between randomization and 12 weeks of 1500 steps per day (SD 2824) in favor of the experimental group compared with the control group, a total of 148 participants (n=74 participants per group [57 plus 17 for attrition], and n=37 per recruitment center) is needed, given a two-sided 5% significance level, power of 80%, and an expected attrition of 23%. The 1500 steps per day is an approximation of half of the recommended daily minutes of moderate intensity physical activity [47]. The attrition of 23% was reported in a meta-analysis of Web-based interventions, in which the experimental groups had an average intervention duration of 13 weeks [17]. The SD of 2824 steps per day was estimated using data found in an RCT of a counseling intervention in ACS patients in Quebec [48].

### Randomization and Allocation

Randomization is planned by an offsite coordinating center. It is stratified by study center to help protect against between group imbalances if recruitment differs in one or more study centers [49]. Per stratum, random numbers are given for each assignment. Random assignments follow a 1:1 allocation using random block sizes determined by the coordinating center to minimize the chance of group imbalances [49].

The assignment sent by the coordinating center in electronic list (.xls) format was uploaded in the TAVIE platform. The allocation sequence is concealed. Upon submission of the baseline questionnaire, the TAVIE platform sends an automated email of the assignment to the participant. This email includes the hyperlink and password to access the experimental TAVIE en m@rche or to receive a different hyperlink to access the control of publicly available websites.

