### Eligibility Criteria

Patients are eligible if they are home the third week after an ACS-related hospitalization, have no serious medical condition that would impede adhering to moderate intensity physical activity, report access in any location to a computer with a USB port that is connected to the Internet, and report the ability to read and speak French. Patients are ineligible if they self-report sufficient physical activity during 6 months prior to the hospitalization where they are recruited (ie, performed at least 150 minutes [30 minutes 5 days a week] of moderate intensity physical activity per week or at least 75 minutes [25 minutes 3 days per week] of vigorous intensity physical activity per week), have documented New York Heart Association Class III-IV heart failure, or reported planned involvement in intensive regular clinical follow-up (eg, an outpatient heart failure clinic) during TAVIE en m@rche. One hospital center asked that those who are eligible for participation in their onsite secondary prevention program (ie, new diagnosis of ACS and age <75 years) be ineligible for study participation to avoid delivery of parallel secondary prevention interventions at that center.

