### Interventions

Both groups receive usual care from hospital entry to return home. At all four recruitment centers, from hospital entry to hospital discharge, usual care consists of brief counseling by hospital staff on discharge issues such as new medications and their side effects and on health behavior changes such as progressively increasing physical activity at home. Printed materials are provided as teaching aids to complement the brief counseling. As well, patients receive referrals to onsite or community-based secondary prevention programs.

After hospitalization, all centers offer secondary prevention programs, but at varying doses. All offer an educational group program on the topic of cardiac risk factors and health behaviors aimed at reducing these risk factors, but the number of sessions varies between one and eight across the four centers. Also, three of the four centers offer onsite supervised exercise programs, but the number of sessions vary between one to three times per week. Two of the programs are 12 weeks in duration, and the other lasts 1 year.

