### Statistical Methods

The Montreal Health Innovations Coordinating Center provided expertise for the statistical methods. Baseline characteristics will be compared using descriptive statistics to identify trends in group imbalances, and the analyses will be consistent with intention-to-treat principles, in which data at a given time point will not be excluded from the analysis [64]. Missing data will be examined and handled according to best practice in that field [65].

For the analyses of single continuous variables (eg, the primary outcome of change in steps per day), repeated measures analysis of covariance models will be used with covariates that include gender, age, diabetes, intermittent claudication, baseline smoking status, depression symptoms, and fatigue. For analyses of multiple continuous variables (eg, the secondary outcomes of change in walking and moderate to vigorous physical activity), repeated measures multivariate analysis of covariance models will be used with the same covariates as the above model. For single dichotomous variables with baseline values (eg, smoking status), sequential logistic regression models will be used. For single dichotomous variables without baseline values (eg, hospitalizations), chi-square models will be used. A mediation analysis will use a sequence of one-way analysis of variance models with Bonferroni adjustments, in which the alpha will be divided by the number of tests performed. Adjusted and unadjusted means or proportions in each group (experimental and control) will be provided along with a 95% confidence interval. No adjustments in *P* values will be made for the hypotheses on secondary and tertiary outcomes because these are aimed at supporting the primary hypothesis on steps per day rather than claiming intervention effect [66].

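### Randomization is stratified by study center, but center is not among the named covariates and the chi-square tests cannot account for it, so precision may be lost

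*Protocol article*

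**What the plan says.** All references are to the protocol article.

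- **Randomization and Allocation.** Study center is the only stratification factor: "It is stratified by study center to help protect against between group imbalances if recruitment differs in one or more study centers". Assignment is 1:1 in random block sizes within each center.
- **Statistical Methods.** The repeated measures analysis of covariance has "covariates that include gender, age, diabetes, intermittent claudication, baseline smoking status, depression symptoms, and fatigue". The multivariate version takes the same list. The logistic models name no covariates. Dichotomous outcomes without a baseline value get a chi-square test. Center is named in none of these, nor in the shorter covariate list in the Abstract.
- **Eligibility Criteria.** Recruitment rules differ by site: "One hospital center asked that those who are eligible for participation in their onsite secondary prevention program" be kept out of the study. That group is patients under 75 with a new diagnosis.
- **Interventions.** Usual care also differs: "three of the four centers offer onsite supervised exercise programs", with different frequencies and lengths, and the educational program runs from one to eight sessions.
- **Sample Size Calculation.** The sample size has no center term: "n=74 participants per group [57 plus 17 for attrition], and n=37 per recruitment center".

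**The concern.** Blocking within center makes the two groups nearly equal in their mix of centers, so differences between centers drop out of the true sampling variation of the treatment difference. A model without center does not know this and keeps those differences in the residual. The standard error it reports then describes a less precise design than the one that was run. Confidence intervals come out too wide, the test rejects less than 5% of the time under the null, and power that the design has already paid for goes unused.

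The size depends on how strongly center predicts the outcome. The site differences in eligibility and in secondary prevention programs make some center effect plausible. Center is also a natural predictor of program attendance, which has no baseline value and so falls under the chi-square rule.

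**Working it through.** **Inputs from the Sample Size Calculation section.** Target difference and SD: "To detect a difference in change between randomization and 12 weeks of 1500 steps per day (SD 2824". Error rates and attrition: "given a two-sided 5% significance level, power of 80%, and an expected attrition of 23"%. Evaluable number: 57 per group, 114 in all.

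**Input not in the protocol.** The share *r* of the variance of 12-week change that center explains. I take *r* = 0%, 2%, 5% and 10% as assumptions.

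**Step 1: reproduce the plan's figure.** A two-sample t calculation with difference 1500 and SD 2824 gives power 79.6% at 56 per group and 80.3% at 57, so 57 is right. Attrition: 57 / (1 − 0.23) = 57 / 0.77 = 74.03, stated as 74; 2 × 74 = 148. The stated sample size reproduces.

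**Step 2: standard error without center.** 2824 × √(2/57) = 529.0 steps per day.

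**Step 3: true standard error under center-balanced allocation.** 529.0 × √(1 − *r*). A model without center therefore overstates it by the factor 1/√(1 − *r*).

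**Step 4: type I error without center.** 2 × [1 − Φ(1.96/√(1 − *r*))]. For *r* = 5%: 1.96/√0.95 = 2.011, giving 4.4%.

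**Step 5: power from the noncentral t, same method for both columns.** The noncentrality is 1500 divided by the true standard error. With center in the model (109 df) the critical value is 1.982. Without it (112 df) the critical value 1.981 is in effect multiplied by 1/√(1 − *r*), because the reported standard error is too large. For *r* = 5%: noncentrality 1500/515.6 = 2.909; effective critical value 1.981/√0.95 = 2.033.

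| *r* (assumed) | True SE | Reported SE too large by | Type I error without center | Power with center | Power without center |
|---|---|---|---|---|---|
| 0% | 529.0 | 0% | 5.0% | 80.3% | 80.3% |
| 2% | 523.7 | 1.0% | 4.8% | 81.0% | 80.5% |
| 5% | 515.6 | 2.6% | 4.4% | 82.2% | 80.9% |
| 10% | 501.8 | 5.4% | 3.9% | 84.2% | 81.5% |

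**Step 6: simulation check.** Four centers, 114 evaluable participants balanced within center, 8000 runs per scenario. Type I error without vs with center was 4.6% vs 4.7% (*r* = 2%), 4.3% vs 5.0% (5%) and 3.8% vs 5.1% (10%). Power without vs with center was 81.0% vs 82.4% (5%) and 81.5% vs 84.1% (10%). Monte Carlo error on a 5% rate is √(0.05 × 0.95/8000) = 0.24 points. At *r* = 0 both models gave about 4.4% to 4.5%, where 5.0% is exact, so I rely on the formulas for type I error. The simulation agrees with them on direction and approximate size.

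**The case against.** The strongest reply is that the covariate list is introduced as a list of inclusions, in a condensed article whose analysis plan is not shown. Center may well be in the full model, and for the logistic models nothing is said either way. This stands in part: a reader might infer that every model is fixed without center, and the text does not go that far. But seven other covariates are spelled out while the one factor that the design imposed is absent, and a plain chi-square of group by outcome cannot take center in at all.

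A reader might also infer that the standard errors are certainly too large, or that the centers are shown to differ in ways that affect steps. The protocol supports neither. It describes differences in eligibility and programs, links none of them to change in steps, and gives no center variance. Several things could make *r* small:

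- Stable center differences in step level largely cancel in a change score.
- Age, already a covariate, may absorb part of the one site's restriction.
- The Introduction puts attendance at face-to-face programs at only 22% to 30%.

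Finally, a reader might infer that planned power is lost. It is not. With the SD held at 2824, power without center stays at or above 80% throughout the table; what is forgone is a gain. The error is also in the safe direction.

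On the chi-square outcomes, it is fair to say that these are exploratory and that events may be rare. With 37 per center, about 28 evaluable after 23% attrition (37 × 0.77 = 28.5), stratified tables could be sparse.

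**Conclusion.** The point holds in conditional form. As written, the analysis does not use the factor by which participants were randomized. If center predicts the outcome, the reported standard errors are too large and the tests conservative. The cost is precision only, and it is modest: none at *r* = 0, rising to a standard error 5.4% too large and about 2.7 points of power at *r* = 10%. The treatment estimate is unbiased, type I error is not inflated, and the 148 participants and 80% power are unaffected.

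The figures rest on the assumed range for *r*, on the total SD of 2824 with no other covariates in the model, and on groups that stay balanced within center among the evaluable. Covariates that overlap with center would shrink the effect, and uneven attrition would make the balance approximate. The change is worth making because it is nearly free and, if stated before the analysis, removes any later choice about center.

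**What to change.** - Add study center (4 levels, 3 df) as a fixed factor to the primary and secondary continuous models and to the logistic models. In the repeated measures form, let center act on the change (center crossed with time); a main effect alone absorbs only stable differences in level.
- For dichotomous outcomes without a baseline value (program attendance, emergency visits, hospitalizations), replace the plain chi-square with a center-stratified Cochran-Mantel-Haenszel test where event counts allow. State in advance what will be done where they do not.
- Write this down before the data are analyzed.

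Cost: 3 of about 110 degrees of freedom for the primary comparison, and possible sparse strata for rare events. No new data are needed and the sample size does not change.

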### Blinding

Care providers during hospitalization (treating physicians, nurses, and others) are blinded to group assignment because randomization occurs posthospitalization. The first author must know of the assignment after it is revealed, in order to manage the emails sent to participants in either the experimental or control group. The outcome data completed online are anonymized allowing blinding to group assignment. Participants are not blinded to group assignment because they consent to randomly receiving one of two website hyperlinks. Although participants are not informed as to which website is experimental versus control, they are informed that one website takes about 60-75 minutes to complete (ie, experimental), and the other website takes an undetermined number of minutes to complete (ie, control).

### Outcomes

#### Primary Outcome of Steps per Day

The primary outcome is change in steps per day measured by an accelerometer between randomization and 12 weeks. We chose 12 weeks as the primary endpoint rather than 5 weeks to assess the persistence of steps performed beyond the end of the intervention’s 4-week period. The accelerometer step count data are concealed, uploaded wirelessly to a server [50], and downloaded in the first author’s computer. Similar to step counts measured by a previously validated pedometer, step counts measured by the accelerometer worn on a shoe had less than 2% error compared with observed step counts measured by hand tally counter [50]. Participants are instructed to clip the accelerometer on one of their shoes during waking hours. If they are not wearing shoes, they are then instructed to clip it at their waistline clothing (belt or pants) as recommended by the manufacturer.

The steps per day mean will be estimated using ≥3 valid step-days within the 7-day wear period, which is an accepted norm in adult populations [51]. A valid step-day will be determined by a wear time of ≥10 hours per day [51]. Fewer than 3 valid step-days will be treated as missing data.

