### Study Aim and Hypotheses

The aim of this RCT is to evaluate in insufficiently active ACS patients, the effect of a fully automated, Web-based tailored nursing intervention (TAVIE en m@rche) on increased steps per day. Our primary hypothesis is that ACS patients in the experimental group receiving TAVIE en m@rche compared with the control group receiving hyperlinks to publicly available websites will demonstrate a greater increase in change in steps per day between randomization and 12 weeks (H1). Secondary hypotheses are a greater increase in change in steps per day between randomization and 5 weeks (H2), and in energy expenditure for walking and moderate to vigorous physical activity between randomization and 5 weeks, and randomization and 12 weeks (H3 to H6).

We are interested in assessing if the change in SDT variables immediately postintervention at 5 weeks will explain the hypothesized increase in steps per day at 12 weeks. Therefore, we will explore the mediating role of the SDT constructs (perceived autonomy support, controlled and autonomous motivations, perceived competence) and barrier self-efficacy on the effect of TAVIE en m@rche on increased steps per day at 12 weeks (H7 to H11 respectively).

We will also explore the effect of TAVIE en m@rche at 12 weeks on improved quality of life (global, emotional, physical, and social), smoking, medication adherence, secondary prevention program attendance, emergency visits, and hospitalizations (H12 to H20). The potential moderating role of sex on the effect of TAVIE en m@rche on steps per day at 12 weeks will also be explored (H21). Finally, we expect no adverse effect, which is represented by an equal level of angina symptom frequency at 12 weeks in both groups (H22).

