#### Experimental Group

The experimental group receives access to TAVIE en m@rche. The central feature of TAVIE en m@rche is the prerecorded videos of a nurse (see Multimedia Appendix 2) who presents the fully automated tailored intervention content delivered according to patients’ baseline assessments of autonomous motivation, perceived competence, and walking behavior. Other modes of delivery include online text that appears beside the videos to allow simultaneous reading of the video’s content, and downloadable PDF files referred to by the nurse. Access to TAVIE en m@rche starts at randomization between the fourth and fifth week after hospitalization, which depends on when the baseline online assessment is submitted. The suggested completion time of the intervention is 4 weeks but access to the intervention ends at 11 weeks postrandomization. An additional brief “booster” is added at 8 weeks postrandomization. We estimate about 60-75 minutes is sufficient to complete the intervention. TAVIE en m@rche consists of 73 videos, each lasting on average nearly 1 minute with most (n=68) lasting less than 2 minutes. The TAVIE platform has simple webpage layouts and is easy to navigate [41].

The intervention goal is to encourage a progressive increase in walking behavior, up to the recommended 150 minutes per week at moderate intensity, which is determined by an adapted version of the Borg Rating of Perceived Exertion [42]. This walking level is recommended to all patients at discharge for an ACS-related hospitalization by their treating physician unless a contraindication is present such as comorbid physical condition or an environmental constraint. Such patients are ineligible for study participation.

The intervention is based on a theoretical framework that integrates SBNC with SDT. SBNC focuses on nursing values such as fostering a collaborative partnership with the person, supporting the person’s self-determination in their decisions and actions, and working with the person’s strengths in the aim of achieving health and healing. The SDT on human motivation specifies theoretical constructs for physical activity to be targeted by the intervention strategies and to drive the tailoring process. The intervention strategies are specifically targeted toward increasing self-reported perceived autonomy support, autonomous motivation, and/or confidence (combined perceived competence and barrier self-efficacy).

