Secondary methods are the use of tailored messages based on “yes” versus “no” responses to questions after intervention login on identifying symptoms of exercise intolerance in the past 7 days (Introduction). Participants who respond “yes” to having identified symptoms of exercise intolerance are provided an onscreen video message asking them to not initiate the intervention, to consult a free 24-hour province-wide phone service for general health problems if the symptoms are nonurgent, or to call 9-1-1 or go to the emergency department if the symptoms are urgent, and then to log out of the intervention. Two weeks later, participants are asked to log in to the intervention, and only if no symptoms of exercise intolerance are identified by the participant, they are invited to continue the intervention. Static tailored messages on walking behavior (ie, feedback on performance) are also provided to participants in all four profiles (Strategy 1 information) based on their responses of walking behavior assessed only at baseline. Other tailored messages based on “yes” versus “no” responses to questions after intervention login pertain to the identification of personal reasons for walking (Strategy 2 reasons), personal strengths (Strategy 3 strengths), personal goals that are SMART (Specific, Measurable, Attainable, Realistic, and within a Timeframe) (Strategy 4 action plan), social support, and solutions to barriers (Strategy 4 action plan).

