Interventions (T1) start immediately after allocation to the experimental or control groups. Follow-ups at 5 weeks (T2) and 12 weeks (T3) postrandomization are planned. At both follow-ups, participants in both groups (experimental and control) are sent an email with instructions to wear the accelerometer for 7 days. If participants accept, a brief text message is sent to remind them to read the email. After 7 days of accelerometer wear, a second email is sent to complete the online questionnaires. In addition, at the end of data collection, participants are instructed to return the accelerometer by mail via the prepaid envelope provided. During participation, the first author is available by phone and email to resolve technical difficulties in accessing the intervention or questionnaires.

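### The 12-week endpoint measures the effect of the whole package (programme, week-8 booster, access to week 11), so it cannot be credited to persistence after a four-week course

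*Protocol article*

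**What the plan says.** All references are to the protocol article.

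- **Rationale for the time point** (Primary Outcome of Steps per Day): week 12 is preferred to week 5 "to assess the persistence of steps performed beyond the end of the intervention". The sentence ends by naming the intervention's four-week period. This is the only reason given for preferring week 12 to week 5.
- **Length of delivery** (Experimental Group): "The suggested completion time of the intervention is 4 weeks but access to the intervention ends at 11 weeks postrandomization". In the same section, the brief booster "is added at 8 weeks postrandomization". The Abstract and Study Design and Settings also describe the experimental arm as the four-week intervention plus the week-8 booster.
- **Deferral** (Experimental Group): participants who report symptoms of exercise intolerance are asked not to begin. "Two weeks later, participants are asked to log in to the intervention", and they continue only if symptom-free.
- **Assessments** (Timeline and Procedures): "Follow-ups at 5 weeks (T2) and 12 weeks (T3) postrandomization are planned". At each, participants "are sent an email with instructions to wear the accelerometer for 7 days". Week 12 is the last assessment.
- **Mediation** (Study Aim and Hypotheses): H7 to H11 ask whether "change in SDT variables immediately postintervention at 5 weeks" explains steps at 12 weeks. Table 2 shows no mediator measured after week 5.

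**The concern.** Persistence means that an effect remains once delivery has stopped. The rationale for week 12 treats delivery as stopping at week 4, whereas the description of the experimental arm has it continuing, through a planned booster and open access, almost until the outcome is measured.

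What is at stake is how the primary result will be read. If the experimental group walks more at week 12, the stated rationale invites the conclusion that a short programme has a lasting effect. The same difference could arise from the booster, from content viewed or reviewed between weeks 5 and 11, or from both. The design has no later measurement and no arm without the booster that would separate these explanations. The Limitations section acknowledges that follow-up is short, but for reasons of feasibility; it does not mention the booster or the continued access.

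The same assumption recurs in the mediation question, where week 5 is treated as the point just after the intervention although the booster and several weeks of access are still to come.

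**Working it through.** **1. The plan's own figure.** Inputs from Sample Size Calculation: difference 1500 steps per day, SD 2824, two-sided 5%, power 80%, attrition 23%.

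- Standardized difference: 1500 / 2824 = 0.531.
- Normal approximation: n = 2 × (1.960 + 0.842)² / 0.531², which rounds up to 56 per group. The two-sample t-test gives 56.6, so 57 per group, with power of about 80.3%.
- Attrition: 57 / (1 - 0.23) = 74.03, taken as 74 per group (57 + 17), and 2 × 74 = 148.

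The stated 148 reproduces. The calculation uses the between-group difference at 12 weeks and does not depend on how that difference is interpreted.

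**2. Time from delivery to the primary outcome.** Interval = 12 minus the week of the delivery event.

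| Delivery event | Week | Interval to week 12 |
|---|---|---|
| Suggested completion of the course | 4 | 12 - 4 = 8 weeks |
| Booster | 8 | 12 - 8 = 4 weeks |
| End of access | 11 | 12 - 11 = 1 week |

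The article does not fix whether the 7-day wear ends at week 12 or starts there. If it ends there, steps are recorded from 11 - 11 = 0 to 12 - 11 = 1 week after access closes. If it starts there, they are recorded from 12 - 11 = 1 to 13 - 11 = 2 weeks after. Hence about 1 week. This is a limit set by access, not an observation of use.

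**3. What is still to come after week 5.** The booster follows 8 - 5 = 3 weeks later, and access continues for 11 - 5 = 6 weeks. A participant who defers for two weeks at the start and then takes the suggested four weeks (an assumption about pace) finishes at week 2 + 4 = 6, after the 5-week assessment. This applies only to those reporting symptoms, and the article gives no figure for how many that would be.

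**4. What a week-12 difference identifies.** Randomization is to the offer of the complete package, so the week-12 comparison estimates the effect of that offer. To attribute the difference to persistence after the four-week course, one would have to assume that the booster and any use after week 4 contribute nothing to steps at week 12. Nothing in the design tests that assumption.

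**5. What the week-5 mediators observe.** They capture changes in autonomy support, motivation, competence and barrier self-efficacy up to week 5. Changes in these constructs produced by the booster or by later use are not measured.

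**The case against.** The case on the other side has real force.

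- **The sentence is literally true.** It refers to the four-week period, and week 12 lies 8 weeks beyond it. A reader might infer that the protocol claims 8 weeks free of exposure; it nowhere says so. This stands, but persistence after a course is informative only if delivery has stopped, and here it has not.
- **The package is disclosed, and the main claims are modest.** The Abstract and Study Design include the booster, Experimental Group gives the access limit, and H1 and the Conclusion speak only of an effect on steps. This stands and confines the defect to the rationale and to any conclusion built on it. Disclosure elsewhere does not make the rationale fit the design.
- **Access is not use.** Total content is estimated at 60-75 minutes, the suggested pace is four weeks, and the booster is brief. A reader might infer that much of the content is taken up after week 4, or that exposure typically ends one week before the outcome. The article gives no usage figures to support either.
- **Week 12 is not empty of information about carry-over.** It can still show a short carry-over, about 4 weeks after the booster or 1 week after access ends. Only persistence after the four-week course is out of reach.
- **Mediation.** A reader might infer that the mediated part of the effect will be understated. That does not follow: motivation and competence at week 5 may themselves determine who returns, uses the booster and keeps walking, so some later effects may lie downstream of the week-5 mediators. The hypotheses are exploratory, and measuring mediators before the outcome suits them. Only the gap in observation is established, not a direction of bias.

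**Conclusion.** The point holds as one of interpretation. The property claimed for the primary time point, that it shows persistence beyond a four-week intervention, is one the design does not have. Week 12 falls 4 weeks after a planned booster and possibly as little as about 1 week after last access, rather than 8 weeks after delivery stopped, and no later assessment exists. The result will estimate the 12-week effect of being offered the whole package.

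A reader might go further and infer that the primary comparison is biased or underpowered. The documents do not support that: the comparison is randomized, and sample size, significance level and power are unchanged.

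The conclusion rests on the stated week numbers and on the ordinary meaning of persistence. The 1-week figure is approximate because the placement of the wear week is not fixed and because access sets only an upper limit on use. For mediation, the conclusion is limited to the fact that changes after week 5 go unobserved. The correction merits making because it concerns the only reason given for choosing the primary time point and costs very little.

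**What to change.** 1. In Primary Outcome of Steps per Day, restate the rationale: week 12 assesses the effect of being offered the four-week programme plus the week-8 booster, with access to week 11. Drop the word persistence, or qualify it as an effect seen after a package whose delivery extends past week 4. Word the trial's conclusions to match.
2. In Study Aim and Hypotheses, qualify the description of week 5 as the point just after the intervention. Add that mediators last measured at week 5 do not observe changes produced by the booster or later use, and that the direction of any effect on the mediation results is unknown.
3. If the platform logs carry dates, report the share of experimental-arm use that falls after week 5. Intervention Adherence lists counts of views and downloads but does not say that they are dated, so this is conditional. It would be a description, not a randomized comparison, and should not be used to recover a persistence claim.

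The cost is a few sentences and, if dates exist, one descriptive table. Delivery, schedule, sample size and primary analysis stay as they are. The downside is a more modest claim.
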